## Abstract

**Background:**

Irritable bowel syndrome (IBS) is a chronic gastrointestinal disorder characterized by abdominal pain and change of bowel habits without organic disease. Many patients seek alternative IBS treatments because of the limitations of conventional treatments. *Gwakhyangjeonggisan *(GJS), a herbal formula, has long been used for alleviating diarrhea-predominant IBS (D-IBS) in traditional medicine. Duolac7S, which comprises 7 bacterial species as probiotics, has been frequently used for D-IBS. Although GJS and Duolac7S have been administered simultaneously in many D-IBS patients, no study has investigated the effects of GJS and Duolac7S combination therapy on D-IBS.

**Methods/Design:**

The current trial is a randomized, double-blinded, placebo-controlled, 4-arm study. After a 2-week run-in period, 60 patients with D-IBS will be randomly assigned to one of the 4 combination groups consisting of GJS (water extract granules, 3 g/pack, 3 times a day) with Duolac7S (powder form, 1 capsule, 2 times a day) or their placebos and followed up for 2 weeks. The assigned treatments will last for 8 weeks. The primary outcomes are adequate relief of IBS pain and discomfort and the proportion of responders (on a weekly basis). The secondary outcomes are visual analog scale for IBS symptoms (on a daily basis), quality of life (at 0, 8, and 10 weeks), intestinal permeability, and composition of intestinal microbiota (at 0 and 8 weeks).

**Discussion:**

The present study is designed to examine the safety and efficacy of GJS and Duolac7S combination therapy on D-IBS. Our study provides the clinical evidence of a new therapeutic strategy for D-IBS.

**Trial registration:**

ClinicalTrials.gov NCT01342718
.

## Background

Irritable bowel syndrome (IBS), a common chronic gastrointestinal disorder characterized by abdominal pain and alteration of bowel habits in the absence of structural abnormality, has a prevalence of approximately 15% in western populations [1,2]. Patients with IBS can be classified by their predominant bowel habits: diarrhea-predominant IBS (D-IBS), constipation-predominant IBS, or IBS with alternating bowel movements [3]. Although smooth-muscle relaxants, bulking agents, and anti-diarrheal agents are commonly used as conventional IBS treatments, many IBS patients turn to alternative treatments because of the lack of therapeutic advantages of these treatments [4]. Therefore, the development of a new therapy is necessary for IBS patients.

*Gwakhyangjeonggisan *(GJS; *Kkako-shoki-san *in Kampo Medicine; *Huoxiang-zhengqi-san *in Traditional Chinese Medicine), which was recorded originally in the famous ancient herbal formula literature *"Formularies of the Bureau of people's Welfare Pharmacies"*, consists of 13 common crude herbs. GJS contains the chemical ingredients naringin, hesperidin, thymol, honokiol, and magnolol [5] and has been shown to protect intestinal barrier function [6], contract the colonic muscle [7], and regulate infectious diarrhea [8]*in vivo*. In traditional Korean medicine, this herbal formula has long been used for relieving abdominal pain, diarrhea, and vomiting as an over-the-counter or prescribed medicine [9-11]. However, there have been no clinical trials to investigate the efficacy of GJS in IBS.

Probiotics are defined as viable microorganisms, which confer potential health benefits on the host when taken in proper amounts [12]. They are easily available, do not require a prescription, and are administered extensively for the relief of abdominal symptoms [13]. According to a recent systematic review and meta-analysis study, probiotics caused a modest improvement in the overall IBS symptoms [14]. The rationale for using probiotics for IBS is based on the assumption that they modify the composition of the intestinal microflora [15] and regulate intestinal permeability by modulating the epithelial tight junctions [16]. Duolac7S, a probiotic mixture, contains 7 bacterial species including *Bifidobacterium, Lactobacillus*, and *Streptococcus*. Each of these bacterial species is reportedly beneficial for IBS [17]. Duolac7S has been approved by the Korean Food and Drug Administration for restoring the ecological balance of intestinal microflora and improving intestinal symptoms [18]. Although Duolac7S has been widely used as an over-the-counter product for IBS-related symptoms, no clinical trials have investigated the efficacy of Duolac7S on IBS.

Recently, several herbal formulas and probiotics have been simultaneously administered to IBS patients for relieving abdominal symptoms [19]. In addition to lack of clinical evidence for the use of GJS or Duolac7S, the efficacy of their combined treatment for IBS has not been elucidated. Thus, there is a need to evaluate the safety and efficacy of administration of GJS, Duolac7S, or a combination therapy as a frequently used treatment for IBS. In the current trial, we will identify the safety and efficacy of GJS, Duolac7S, or a combination therapy on D-IBS by evaluating IBS symptoms and quality of life. To investigate their mechanisms in humans, intestinal permeability and composition of intestinal microbiota will be assessed.

## Materials and methods

### Objectives

The aims of the study are as follows: (1) to verify the effect of GJS combined with Duolac7S on D-IBS; and (2) to analyze mechanisms and establish scientific evidence for the use of GJS with Duolac7S by investigating changes in intestinal permeability and the composition of intestinal microbiota.

### Hypothesis

We hypothesize the following possibilities: (1) GJS combined with Duolac7S will show more beneficial effects on D-IBS symptoms than either GJS or Duolac7S alone; and (2) after 8 weeks of administration of GJS with Duolac7S, intestinal permeability will be lowered and the proportion of lactic acid bacteria in the intestine will be changed.

### Design

The current study will be conducted as a placebo-controlled and double-blind trial with 60 patients being randomly allocated to 4 arms. The trial will be implemented at Kyung Hee University Hospital at Gangdong in Seoul, Korea.

Participants will be required to pursue a 2-week run-in (weeks -2 to 0), 8-week administration (weeks 0 to 8), and a 2-week follow-up period (weeks 8 to 10) and to record daily symptoms in a diary.

During the administration period, 1 pack 3 times a day (2 h after each meal) of GJS or its placebo and 1 capsule 2 times a day (2 h after breakfast and dinner) of Duolac7S or its placebo will be provided for 8 weeks. All participants will be divided into 4 groups: (1) the real GJS and real Duolac7S group; (2) the real GJS and placebo Duolac7S group; (3) the placebo GJS and real Duolac7S group; and (4) the placebo GJS and placebo Duolac7S group. The flow of the entire trial is shown in Figure 1.

**Figure 1 F1:**
[figure not shown]
**Flow chart of trial**. D-IBS: Diarrhea-prediminant irritable bowel syndrome. GJS: *Gwakhyangjeonggisan*. DUO: Duolac7S. GJS-P: Placebo of *Gwakhyangjeonggisan*. DUO-P: Placebo of Duolac7S

The current study will be performed in accordance with the standards of the International Committee on Harmonization on Good Clinical Practice and the revised version of the Declaration of Helsinki. The protocol of the trial has been approved by the institutional review boards (IRBs) and ethics committee of Kyung Hee University Hospital at Gangdong. The permission number of IRBs is KHNMC-OH-IRB 2010-011, and the protocol identification number of ClinicalTrials.gov is NCT01342718. Written informed consent will be obtained from all participants prior to enrollment and patients will be given adequate time to decide if they wish to participate before signing the consent form.

### Sample size calculation

The present trial has a pilot character of a new therapeutic strategy of GJS and Duolac7S. Similar to the results of a previous study, 12 participants who complete the study can be considered minimal clinical significance [20]. The drop-out ratio is assumed to be 20%. Ultimately, each group will consist of at least 15 participants so the total sample size should be more than 60 participants. This sample size is determined to provide 80% power to demonstrate the superiority of the study agents compared to placebos and a *P*-value < 0.05 will be considered statistically significant.

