The current study has several distinctive features. First, to the best of our knowledge, this will be the first trial to investigate the efficacy of GJS and Duolac7S combination therapy on D-IBS. In spite of the beneficial effects of GJS on IBS in traditional medicine, treatment of IBS by GJS has not been evaluated in clinical trials. No studies have targeted Duolac7S, a mixture of 7 lactic acid bacterial species, as a treatment for D-IBS; however, several studies have suggested that the individual bacterial species in Doulac7S and other probiotics mixtures may improve IBS symptoms. Moreover, GJS and Duolac7S combination therapy has never been the subject of a previous study. Thus, it is expected that the present trial will provide evidence for the effective application of GJS and Duolac7S combination therapy in D-IBS. Second, the participants in the current trial will be grouped into 4 arms. Test groups in this study will be divided into 4 arms in order to identify the efficacy of the combination therapy and to compare each treatment's effect. Ultimately, the combination therapy of GJS and Duolac7S are postulated to generate a synergistic effect resulting in greater improvement of D-IBS symptoms than individual GJS or Duolac7S treatment. Third, we will conduct analyses of intestinal permeability and the composition of intestinal microbiota after administration of GJS with Duolac7S. The urine and stool analysis results could provide evidence for the combination treatment and the possible mechanisms might also be investigated.

Although our study has a relatively small sample size for a pilot study, our trial is considered to have creative and challenging characteristics and is expected to play an important role in providing basic clinical data in the field of herbs and probiotics and developing methodology in IBS studies.

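### The 80% power claimed for 15 patients per arm has no effect size behind it and would hold only for very large effects

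*Protocol article*

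**What the plan says.** The Sample size calculation section of the protocol article describes the trial as a pilot of a new treatment strategy. It then gives the size in three steps.

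- The starting number is taken from a previous study: "12 participants who complete the study can be considered minimal clinical significance".
- Dropout is added: "The drop-out ratio is assumed to be 20" percent, giving at least 15 per group and 60 in all.
- A power is then attached: "This sample size is determined to provide 80% power to demonstrate the superiority of the study agents compared to placebos", with the significance rule that a P "value < 0.05 will be considered statistically significant".

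The Hypothesis section puts the main clinical question differently: "GJS combined with Duolac7S will show more beneficial effects on D-IBS symptoms than either GJS or Duolac7S alone". The Discussion returns to the pilot description: "Although our study has a relatively small sample size for a pilot study".

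The primary outcomes are weekly adequate relief (yes/no) and the proportion of responders. The article gives no expected responder rate, difference or standard deviation for any outcome.

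**The concern.** The text shows how the number was reached: precedent plus an allowance for dropout. That route does not produce a power. The next sentence nevertheless says that the size was determined by an 80% power requirement. The two accounts of the same number do not agree, and the pilot label sits badly with a powered superiority claim at P < 0.05.

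The contrast is a second mismatch. The power is claimed for study agents against placebos, while the main hypothesis compares the combination with each single agent. No power is claimed for the question that the trial puts first.

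What is at stake is how the result is read. If 80% power is taken at face value, a non-significant comparison could be read as evidence that the treatments do not work, and a P value below 0.05 as confirmation that they do. A trial of this size supports neither reading unless the true effects are very large.

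**Working it through.** **Inputs from the article.** 12 completers per arm; 20% dropout; 15 randomised per arm; four arms in a 2x2 layout; significance level 0.05; stated power 80%; binary primary outcome.

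**Assumptions, because the article gives no value.** Two-sided testing. Control responder rate 30% for the main table, with 20% to 50% as the range. An uncorrected chi-square or Fisher exact test for responders, and a two-sample t-test for a continuous outcome.

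**Step 1: the article's own arithmetic.** 12 / (1 - 0.20) = 15, and 4 x 15 = 60. This reproduces.

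**Step 2: the 80%.** It cannot be recomputed, because there is no effect to put into the formula. The calculation can only be turned round, to find the effect that would give 80%.

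- Responders: power is the sum, over all pairs of counts (a, b) that the test rejects, of Bin(a; n, p1) x Bin(b; n, p2). The treated rate p2 is raised until power reaches 80%.
- Continuous outcome: noncentral t with 2n - 2 degrees of freedom and noncentrality d x sqrt(n/2), solved for d.

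| Reading of the comparison | n per side | Treated rate needed against 30% (chi-square / Fisher) | d needed |
|---|---|---|---|
| Two arms, completers | 12 | 82% / 89% | 1.20 |
| Two arms, all randomised | 15 | 80% / 86% | 1.06 |
| 2x2 margin, completers | 24 | 69% / 73% | 0.83 |
| 2x2 margin, all randomised | 30 | 66% / 69% | 0.74 |

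Against 30%, the two-arm differences are 50 to 59 points and the margin differences 36 to 43 points.

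**Step 3: sensitivity to the control rate.** With 12 per arm, the normal approximation gives 20% vs 75%, 30% vs 84%, 40% vs 92% and 50% vs 98%. The differences are 55, 54, 52 and 48 points, so the choice of control rate does not drive the conclusion. One-sided testing lowers the requirement only to 30% vs 79% and 40% vs 87%.

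**Step 4: power at smaller differences, 12 per arm (chi-square / Fisher).** 40% vs 60%: 19% / 10%. 40% vs 70%: 36% / 21%. A true 20-point difference would be missed 81% to 90% of the time.

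**Step 5: the size that would give 80% for 20 points.** n = [1.96 x sqrt(2 x pbar x (1 - pbar)) + 0.8416 x sqrt(p1(1 - p1) + p2(1 - p2))]^2 / (p2 - p1)^2.

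- 30% vs 50%: (1.358 + 0.571)^2 / 0.04 = 93 completers per arm; 93 / 0.8 rounds up to 117 randomised.
- 40% vs 60%: (1.386 + 0.583)^2 / 0.04 = 97 completers per arm; 97 / 0.8 rounds up to 122 randomised.

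**Step 6: what the planned size does deliver.** 95% half-widths at a 50% rate:

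- One arm: 1.96 x sqrt(0.25/12) = 0.28; with 15, 0.25.
- Difference between two arms: 1.96 x sqrt(0.5/12) = 0.40; with 15, 0.36.

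**The case against.** Five points can be made for the article.

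1. **The 80% cannot be shown to be wrong.** Some effect size always gives 80% power, and the only arithmetic on the page is correct. This stands. A reader might infer that the article contains a calculation error, or that the design certainly lacks the stated power. With no effect given, the documents support only that the figure is unsupported and implies a very large effect.

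2. **The effect assumption may lie in the cited study or the full protocol.** It may, and its absence from a condensed article would not by itself be a finding. But the article does state how 12 was chosen, and then credits that number with a power that the stated route does not yield. The objection is to what is written.

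3. **The 12 versus 12 reading is the harshest.** This is fair. Agents against placebos can mean the 2x2 margins, and an intention-to-treat analysis is planned, so 30 versus 30 is a legitimate reading. It lowers the requirement to about 36 points or d = 0.74. That is still large, and the margins do not serve the main hypothesis, because combination against a single agent remains one arm against one arm. Nor should the 12-per-arm requirement be called near-total separation: 30% against 82% is very large but not that.

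4. **The test is not the planned one.** The Statistical analysis section names repeated measures ANOVA for the four-group comparison and mentions chi-square only for baseline and patient characteristics. The responder powers above are therefore illustrations for the binary outcome. The standardised differences give the continuous counterpart for a simple two-group test, and they are large as well.

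5. **The pilot label protects the reader.** It helps, and so does the Discussion's admission of a small sample. For that reason one cannot say that a null result would be misread, only that it could be. The label does not cancel an explicit power and superiority claim in the same section.

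A reader might also infer that the combination-versus-single-agent effect must be smaller than the effect against placebo. The documents do not say so; the Discussion postulates synergy. Only the mismatch of contrasts is established.

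**Conclusion.** The point holds in this form: the 80% power is asserted for a size that the article itself derives from precedent and dropout, no effect size supports it, and the contrast it names is not the main hypothesis. The claim would be true only for differences of about 50 points or more between two arms, or about 36 to 43 points on the 2x2 margins, at an assumed 30% control rate and two-sided 5%. The matching standardised differences are 1.06 to 1.20 and 0.74 to 0.83. The Background itself describes the pooled benefit of probiotics on overall symptoms as modest, which gives no ground for expecting effects of that order from the probiotic component; it says nothing comparable about the herbal formula.

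The responder rates, sidedness and tests are assumptions. The conclusion does not depend on the particular choice, since every variant tried needs a large effect. The consequence is one of interpretation: a non-significant result could be taken as evidence of no effect when the trial had little chance of detecting a 20 or 30 point difference between two arms.

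**What to change.** Delete the 80% power sentence from the Sample size calculation section and replace it with text to this effect:

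- Fifteen patients per arm (12 completers after 20% dropout) is a pilot size based on precedent and feasibility.
- Assuming a 30% control responder rate and two-sided 5%, 80% power exists only for differences of about 50 points or more between two arms, and of about 36 to 43 points on the 2x2 margins.
- At a 50% responder rate, the expected 95% confidence interval half-width is about 25 to 28 points for one arm and 36 to 40 points for a difference between two arms (15 and 12 per arm).
- Results will be reported as estimates with confidence intervals, and P < 0.05 will be treated as exploratory.

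If a powered claim is to be kept, the section must instead state the primary contrast, responder rates, sidedness and test, and the number must be recomputed. For a 20-point difference between two arms, that means about 117 to 122 randomised per arm.

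The recommended change costs wording only. The stated design property becomes less favourable, and no patients, visits or randomisation steps change. Recruitment, already under way according to the Trial status section, is not affected.

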### Inclusion criteria

Patients aged 18-75 years with consistent abdominal pain and discomfort should meet the Rome III criteria of IBS [3]. Among IBS subtypes, participants must also be included in the D-IBS type, defined as loose (mushy) or watery stools ≥ 25% and hard or lumpy stools < 25% of bowel movements [3]. The Bristol scale, which is a visual descriptive stool form scale, will be used to assess stool consistency [21]. Patients should not have had structural abnormalities in their intestine detected by colonoscopy in the past 5 years.

### Exclusion criteria

Patients who report the following conditions will be excluded: (1) history of abdominal surgery which was related to IBS symptoms; (2) alarm symptoms such as severe weight loss in the past month, melena, and dysphagia; (3) gastrointestinal organic lesions such as cholangitis, pancreatitis, enteritis, and ulcer; and (4) severe systemic organ diseases such as cancer. All participants will have to undergo routine tests of complete blood count (CBC), kidney function (blood urea nitrogen and serum creatinine), liver function (serum aspartate transaminase and alanine transaminase), thyroid function (thyroid stimulating hormone), serum C-reactive protein (CRP), and stool occult blood in order to exclude those who have infection or serious organ diseases. Women with childbearing potential will be required to have a negative pregnancy urine test. Patients who have taken antibiotics, herbal medicine, or probiotics 2 weeks prior to screening will also be excluded.

### Recruitment

Information will be sent by mail to patients with IBS who were previously identified at the Kyung Hee University Hospital at Gangdong, and public advertisements will be placed in the newspaper to recruit participants. Colored fliers, brochures, and banners have been placed inside the hospital. We also plan to place advertisements on the homepage of the hospital and the boards of social networks like Twitter.

### Randomization

Randomization will be performed by an independent statistician by generating allocation numbers by using a random number creation program. The investigator will be notified of the number assigned to a participant via fax or e-mail.

### Blinding

The patients will be blinded to the treatment they are provided. The investigator, clinical research coordinator, and clinical pharmacist will also be blinded to randomization. Only the independent statistician will be associated with the randomization, and the entire procedure will be monitored by the authorized clinical research organization (CRO), Marinet Corporation, Seoul, Korea.

### Interventions

GJS, a famous herbal formula in Korea, has been traditionally used for managing various gastrointestinal dysfunctions including diarrhea, abdominal pain, and discomfort [9-11].

The GJS that will be used in this study is a brown, bitter herbal extract granule (Gwakjungsan granule^®^, Hanpoong Pharm & Food Co., Ltd., Jeonju, Korea) produced in accordance with the Korean Good Manufacturing Practice. Gwakjungsan granule^® ^(GJG), a water-extracted GJS mixed with starch and lactose, is allowed and regulated by the Korean Food & Drug Administration. Each GJG contains the 13 herbs listed in Table 1. All herbs will be obtained from qualified suppliers in Korea and the GJG will be sealed in opaque aluminum bags. Placebo GJG, made with cornstarch powder with the same color and taste as GJG, will be packed identically to the active herbal formula in opaque aluminum bags with the same labeling as real GJG. All packages will be dispensed by an independent pharmacist in a separate room. Patients will be requested to dissolve GJG or placebo granules in each package using water and take them 2 h after each meal. Voucher specimens of GJG will be retained at the research laboratory of the manufacturer.

**Table 1 T1:** Ingredients of herbal formula (*Gwakhyangjeonggisan*)

Scientific name	Parts of use	Gram/day
*Agastache rugosa*	Above-ground parts	1.0
*Perilla frutescens*	Leaves and twigs	1.0
*Angelica dahurica*	Root	1.5
*Areca catechu*	Peel	1.0
*Poria cocos*	Dried core	3.0
*Magnolia officinalis*	Peel	2.0
*Atractylodes macrocephala*	Peel and rhizome	3.0
*Citrus unshiu*	Peel	2.0
*Pinellia ternate*	Stem	3.0
*Platycodon grandiflorum*	Root and peel	1.5
*Glycyrrhiza uralensis*	Rhizome	1.0
*Zingiber officinale*	Rhizome	1.0
*Ziziphus Jujuba*	Fruit	2.0

Duolac7S (Cell Biotech Co., Ltd., Gimpo, Korea) is a probiotic mixture containing multiple strains of 3 viable bacteria species: 3 strains of *Bifidobacterium *(*B. brevis, B. lactis and B. longum*); 3 strains of *Lactobacillus *(*L. acidophilus, L. plantarum, and L. rhamnosus*); and 1 strain of *Streptococcus *(*S. thermophilus*). Duolac7S will be contained in the capsule form with each capsule containing 5 billion bacteria in the powder form. Placebo Duolac7S, a powder consisting of cornstarch with the same color and taste as Duolac7S, will be contained in a capsule identical to the study agent. Patients will swallow 1 capsule of Duolac7S or placebo 2 h after breakfast and dinner for the 8-week administration period. At the end of the study, participants will be asked whether the herbal formula or probiotic that was administered was real or whether it was a placebo to evaluate the success of blinding.

Compliance will be checked by counting returned GJG or Duolac7S. A patient's data will be excluded from *per-protocol *analysis unless compliance reaches at least more than 60% of each GJG and Duolac7S.

All participants will be asked to record any adverse events in their diary during administration and the follow-up period. The CBC, CRP, renal function, and liver function will be assessed to determine the safety of treatments after the administration period. Analyses will be undertaken at an accredited laboratory. All values detected in the laboratory will be recorded by the investigator in the case report form.

